### Primary analyses

Preliminary analyses will summarize characteristics of the intervention and control women and assess frequency distributions of variables to identify outlying or unusual values. Initial analyses of our primary outcomes of maternal ART adherence and maternal retention in care (dichotomous variables) will be based on comparisons of proportions between intervention and control groups using cluster-adjusted chi square tests. Although there are only 24 clusters, each mean or percentage will be based on a relatively large number of women, and the normal approximation to the binomial distribution can be used. These tests will be evaluated based on a two-sided alternative hypothesis with a 5% type I error rate. Given the clustered study design, generalized estimating equation (GEE) models will be used to test for differences of interest in univariate and multi-variable models, adjusted for relevant covariates (such as time on ART), using logistic links for these binary outcomes. Secondary outcomes, such as time to infant testing uptake, maternal viral load suppression, and changes in maternal CD4 counts, will be analyzed using similar methods, taking into account the nature of the dependent variable (continuous, dichotomous, or time to event). Results will be summarized as odds ratios for models based on binary responses (e.g., enrollment in HIV care), hazard ratios for time-to-event outcomes (e.g., time to infant HIV test), and mean changes for continuous responses (e.g., maternal CD4 count); respective 95% confidence intervals will also be reported based on the robust variance estimates from the GEE models.

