### Study design

This study is a cluster randomized, factorial, controlled trial. Using a 2 × 2 factorial design, we will evaluate the effect of cMMs, text messaging, or both on service utilization and maternal and child health outcome indicators. Study sites will be randomized into one of four groups: six sites will implement both interventions, six sites will implement the cMM intervention only, six sites will implement the mobile phone text message intervention only, and six sites will implement the existing standard of care only (Fig. 1). Randomization will be stratified by geographic region such that each unique geographic region will have at least one site in each study arm. The study employs a unique participatory community randomization approach. Site representatives and key stakeholders will be invited to a centralized randomization meeting in which a representative from each site chooses a sealed opaque envelope from a jar; the envelope reveals their site’s randomization arm.

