### Power and sample size estimation

We have powered this study based on differences in proportions in a cluster randomized trial for our key outcomes of maternal ART adherence (percentage of women who report at least 85% adherence) and maternal retention in care (proportion of women with visit within 90 days) at 12 months postpartum. Our sample size and power estimates are based on both clinical and logistic factors. Current estimates on required adherence to non-nucleoside-based regimens are estimated to be 75–80% [29–31]. Additionally, current standard HIV clinic forms in use in Kenya define good adherence as > 95% adherence, fair adherence as 85–94% adherence, and poor adherence as < 85% adherence based on number of missed doses. Power calculations were made based on estimated differences in these rates in the intervention versus the control arms of the study, using appropriate methods for clustered data [32]. We estimated a baseline ART adherence rate of 55% based on current rates found in the literature for sub-Saharan Africa [33] and a baseline retention in care rate of 48% based on data from our recent trial of service integration conducted in the same region in Kenya [26]. We powered our study to be able to detect a 25% absolute increase in ART adherence due to each intervention individually. Given that the actual intracluster correlation coefficients (ICCs) are not known for these outcomes and are not easily specified, we calculated the number of communities needed for ICCs ranging from 0.06–0.12 for 80% power with a two-sided alpha of 0.05, for a fixed average cluster size (Table 1). To achieve 80% power for detecting a significant difference in the proportion who are at least 85% adherent at 12 months, from 55% in the control arm versus 80% in the intervention arm (two-sided *p* < 0.05), with a conservative (high) ICC of 0.12 and an average of 70 women sampled per community (an estimated minimum of 50 and maximum of 130 women per cluster), we would need 18 communities, 4.5 in each arm of the trial. For retention in care, to achieve 80% power to detect a significant difference in the proportion who have an HIV care visit within 90 days of the 12 months postpartum date, from an estimated 48% in the control arm versus 73% in the intervention arm (two-sided *p* < 0.05), with a conservative (high) ICC of 0.12 and an average of 70 women sampled per community (50—130 women per cluster), we would need 20 communities, 5 in each arm of the trial. This sample size will power us to evaluate both of our primary outcomes. It is conservative due to the high ICC estimate and thus should also be sufficient if we experience loss to follow-up. This will result in a target sample size of 1336 women (334 women per arm).

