The use of the 2 × 2 factorial design will allow us to examine the individual effects of each intervention, as well as the potential combined effects when both interventions are introduced in the same community. Although the interventions we will test alone and in combination have been used in sub-Saharan Africa and are evidence-based, we will include some novel aspects that our prior research suggests will make these interventions even more effective. These include basing mentor mothers in the community rather than at the health facility and focusing their activities on HIV prevention and treatment behaviors as well as support for adherence and retention among women and children. Similarly, our mobile phone intervention will extend beyond the short-term interventions that have previously been tested for PMTCT to continue for a minimum of 12 months and will include unique theory-based content as well as bi-directional communication to support long-term adherence and retention.

Our study has a number of limitations. First, it is being conducted in an environment where study sites are implementing other interventions simultaneously. This might attenuate the effect of our intervention. Second, policy and service changes are constantly occurring within the PMTCT field which might interact with our intervention in unknown ways. However, we feel that operating in an environment with other simultaneous interventions and changing policies reflects “real-world” implementation of our interventions and therefore enhances external validity. Finally, our study relies on medical records and a single-item self-report of ART adherence. This method carries biases that might result in inaccurate measurement of medication adherence. To address this limitation, we will also measure HIV viral load, which is a biological measure that is less prone to bias.

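### The two-group chi-square and univariate GEE planned for the primary outcomes have no place for the other randomised intervention, so on the factorial margins they are conservative and lose power

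*Protocol article*

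**What the plan says.** Study design sets out four arms of six sites each: "six sites will implement both interventions, six sites will implement the cMM intervention only", and six each for text messaging only and standard care. The Discussion says that the factorial layout is there to "examine the individual effects of each intervention, as well as the potential combined effects".

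Power and sample size estimation treats the trial as a plain two-group comparison with "80% power with a two-sided alpha of 0.05". It aims to "detect a 25% absolute increase in ART adherence due to each intervention individually". Adherence is taken "from 55% in the control arm versus 80% in the intervention arm" and retention "from an estimated 48% in the control arm versus 73% in the intervention arm", in each case "with a conservative (high) ICC of 0.12 and an average of 70 women sampled per community". No rate is given for sites that receive both interventions.

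Primary analyses then describes the initial analyses of both primary outcomes as "comparisons of proportions between intervention and control groups using cluster-adjusted chi square tests", at a two-sided 5% level. The same paragraph adds univariate and multivariable GEE models with a logistic link. Time on ART is the only covariate given as an example, and confidence intervals are to come from the robust GEE variance. The other intervention is neither named as a stratum or model term nor ruled out as one.

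**The concern.** Each factorial margin mixes two kinds of site. In the text v no-text comparison, half the sites on each side also have cMMs. If cMMs work, those sites differ systematically from their neighbours on the same side. A test without a cMM term sees that difference as unexplained variation between sites, which raises the estimated ICC and the standard error.

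In an individually randomised factorial trial with binary outcomes this matters little. In a cluster trial it matters more, because the site is the unit of variation and there are only 12 on each side. At stake is efficiency: a real effect of either intervention is more likely to be missed, and most likely when the other one also works, which is what the design hopes for.

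**Working it through.** **1. Reproduce the plan's own figure.** Inputs from Power and sample size estimation and Table 1: 48% v 73% and 55% v 80%, two-sided α 0.05, 80% power, mean cluster size 70, ICC 0.12, cluster range 50 to 130. Assumption: coefficient of variation of cluster size = range/4 divided by the mean = (130 − 50)/4/70 = 0.286.

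- The two-proportion formula with continuity correction gives 67 women per side for retention and 62 for adherence.
- Design effect = 1 + [(1 + 0.286²) × 70 − 1] × 0.12 = 9.966.
- Retention: 2 × 67 × 9.966 = 1335 (plan: 1336). Adherence: 2 × 62 × 9.966 = 1236 (plan: 1236). All 14 rows of Table 1 come within one woman.

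So the 1336 is two groups of 668, which are the factorial margins (2 × 334). The calculation contains nothing for the other factor.

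**2. Assume a combined-arm rate.** Two cases:

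- *Additive on the logit scale.* Retention odds = 2.704²/0.923 = 7.92, so 88.8%. Adherence odds = 4²/1.222 = 13.09, so 92.9%. The other intervention is then worth 25 points at one level and 15.8 (retention) or 12.9 (adherence) at the other.
- *Additive on the risk scale.* Retention 98%. Adherence would be 105%, which is impossible, so it is capped at 100% in the formula and 99% in simulation.

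**3. Power for one margin, retention, logit-additive, 24 sites, 1336 women, ICC 0.12.**

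- Mean site size m = 1336/24 = 55.67; allowing for unequal sizes, 55.67 × 1.0816 = 60.21. Inflation = 1 + 59.21 × 0.12 = 8.105.
- Site-level variance w(p) = p(1 − p) × 8.105/55.67: 0.0363 at 48%, 0.0287 at 73%, 0.0145 at 88.8%.
- v = (0.0363 + 2 × 0.0287 + 0.0145)/2 = 0.0541. SE with the other factor accounted for = √(0.0541/12) = 0.0672.
- Extra spread counted as noise without it: (0.25/2)² + (0.158/2)² = 0.0219; × 12/11 = 0.0238. SE used by the two-group test = √[(0.0541 + 0.0238)/12] = 0.0806, which is 20% larger.
- Marginal effect d = (0.888 − 0.48)/2 = 0.204.
- Power with the other factor = Φ(0.204/0.0672 − 1.96) = 85.9%.
- Power without it = Φ[(0.204 − 1.96 × 0.0806)/0.0672] = 75.3%. The divisor stays at 0.0672 because the other factor is balanced by design, so the estimate itself is no more variable; only its standard error is overstated.

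**4. All cases at 24 sites and 1336 women.** Power with v without the other factor. The simulations are 8000 beta-binomial trials each, with an ICC-adjusted chi-square.

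| Case | ICC | Formula | Simulation |
|---|---|---|---|
| Retention, logit | 0.12 | 85.9 v 75.3% | 84.7 v 73.1% |
| Adherence, logit | 0.12 | 86.4 v 75.2% | 85.7 v 73.3% |
| Retention, risk scale | 0.12 | 97.6 v 91.6% | 97.0 v 88.1% |
| Adherence, risk scale (capped) | 0.12 | 97.0 v 90.3% | 95.6 v 86.1% |
| Retention, logit | 0.06 | 98.2 v 92.4% | 97.5 v 90.0% |
| Adherence, logit | 0.06 | 98.3 v 92.3% | 97.7 v 90.5% |
| Retention, risk scale | 0.06 | 100.0 v 99.0% | 99.9 v 96.9% |
| Adherence, risk scale (capped) | 0.06 | 99.9 v 98.6% | 99.8 v 96.5% |

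A separate simulation (20,000 trials, site-level model with both factors, logit-additive, ICC 0.12) gave 83.9 v 73.4% for retention and 84.7 v 74.1% for adherence.

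**5. Type I error.** With the tested factor null and the other working as planned, at ICC 0.12, the two-group chi-square rejected in 2.3% (retention) and 1.9% (adherence) of simulated trials. The stratified version rejected in 5.9% and 6.5%. It is thus slightly liberal, which accounts for part of the simulated gap in step 4. The formula and the site-level model put the loss at 10.5 to 11.2 points.

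**The case against.** The strongest reply is that the chi-square is only the initial analysis. The reported intervals come from the GEE, nothing stops the multivariable GEE from carrying both factors, and the list of model terms commonly sits in an analysis plan that is not shown. The Discussion also commits to separate and combined effects. This stands, and it limits the point. A reader might infer that the trial's primary inference ignores the second factor, and the article does not show that. What remains is that the two tests which are fixed in form, the two-group chi-square and the univariate GEE, leave the factor out by construction.

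Other stronger readings also fail:

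- *A flat loss of 11 points, or an underpowered trial.* Eleven points is one scenario. It needs the ICC that the plan itself calls conservative, and logit-additive effects that the plan does not state. With risk-scale effects, or at ICC 0.06, the two-group test stays above 80%.
- *Wrong or biased results.* The other factor is balanced across the margins, so the marginal difference is not biased by leaving it out. The standard error is too large and the test errs on the safe side.
- *Any active arm v standard care, 18 v 6 sites.* The wording of the test allows it, but the plan powers each intervention individually and its total reproduces as two groups of 668. Both point to the margins.

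**Conclusion.** The point holds as one of efficiency. The two-group chi-square and the univariate GEE, run on the 12 v 12 margins, treat a randomised and known source of variation as noise. At 24 sites, 1336 women and ICC 0.12 this costs about 11 points of power under logit-additive effects, moving the test from above the 80% target to below it. Under risk-scale effects it costs about 6 to 9.5 points with power still above target, and at ICC 0.06 about 1 to 7.5 points. There is no loss if the other intervention does nothing.

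These figures rest on an assumed combined-arm rate, both interventions working as planned, a cluster-size variation inferred from the stated range, and no loss to follow-up, although the article allows for up to 20%. The logit case is a reasonable base, since strict risk additivity is impossible for adherence and the planned GEE uses a logistic link.

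**What to change.** For each primary outcome, name one main analysis: a GEE with text (yes/no) and cMM (yes/no) both as terms, each main effect read with the other in the model. Test text × cMM second and report the four arm-specific rates. Keep the two-group chi-square and the univariate GEE as descriptive. State the assumed combined-arm rate and give the power for this model. The simulated type I error of about 6% for the stratified test suggests choosing a variance estimate or reference distribution suited to 24 sites.

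The cost is one extra model term (1 df) and some wording, with no new data. The Trial status section puts the study at month 44 of 60, so this could be settled before the final analysis.

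### Many women per site do not justify the normal approximation with 24 randomised sites: the nominal 5% is about 6-7% for the main-effect chi-square, and more for GEE if left uncorrected

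*Protocol article*

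**What the plan says.** The Study design section randomises 24 sites equally to four arms: "six sites will implement both interventions, six sites will implement the cMM intervention only", and six each to text messaging only and to standard care.

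The Primary analyses section begins with "comparisons of proportions between intervention and control groups using cluster-adjusted chi square tests" for the two primary outcomes, adherence and retention. It then opens a sentence with "Although there are only 24 clusters" and concludes that this does not matter, because each percentage is "based on a relatively large number of women, and the normal approximation to the binomial distribution can be used". The next sentence reads: "These tests will be evaluated based on a two-sided alternative hypothesis with a 5% type I error rate". In context, both the argument and the 5% belong to the chi-square tests.

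Logistic GEE models come next, introduced separately because the design is clustered. For their estimates, "respective 95% confidence intervals will also be reported based on the robust variance estimates from the GEE models". The section names no small-sample correction, no reference distribution and no working correlation for GEE, and it does not say which version of the adjusted chi-square is meant.

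**The concern.** The argument counts the wrong units. The number of women per site governs how closely one site's observed proportion tracks that site's own rate. The test compares arms, and its error comes mostly from differences between sites. That variance is estimated from 24 sites, or 12 for a pair of arms. A chi-square reference on one degree of freedom treats it as known. A sandwich variance that is not corrected for few clusters is in addition biased downward.

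If the plan is followed as written, primary p-values can be too small and 95% intervals too narrow. The arm-level contrasts, which use only 12 sites, are hit hardest. They matter because the Discussion promises the separate and combined effectiveness of the two interventions.

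**Working it through.** **Inputs.** From the protocol: 24 sites, six per arm; two-sided 5%; ICC 0.06 to 0.12; 50 to 130 women per site, planned mean 70; 1336 women in total; 55% v 80% adherence and 48% v 73% retention. Derived: 1336/24 = 55.7 women per site; coefficient of variation of site size, taken as range/4 over the mean, (130 - 50)/4/70 = 0.286.

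**Reproducing the plan's own figures.** The two-proportion formula with continuity correction gives 61.6, so 62 per group, for adherence and 66.6, so 67 per group, for retention. The design effect is 1 + ((1 + CV²) × 70 - 1) × ICC. At ICC 0.12 it is 1 + (1.0816 × 70 - 1) × 0.12 = 9.966.

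- Adherence: 2 × 62 × 9.966 = 1235.7 (stated 1236).
- Retention: 2 × 67 × 9.966 = 1335.4 (stated 1336).

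All 14 totals in Table 1 reproduce to within 2 women, so the design inputs are read correctly.

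**Why more women do not help.** In units of p(1 - p), the variance of one site's proportion is ICC + (1 - ICC)/m. With m = 55.7:

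- ICC 0.06: 0.06 + 0.94/55.7 = 0.0769, of which 78% is between-site.
- ICC 0.12: 0.12 + 0.88/55.7 = 0.1358, of which 88% is between-site.

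Even unlimited women per site would leave the between-site part, estimated from the same number of sites.

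**Analytic approximation (equal site sizes).** With K sites compared in two groups, the variance estimate carries K - 2 degrees of freedom.

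- Unbiased variance, chi-square(1) reference: error = 2P(t on K-2 df > 1.96). This is 6.3% for K = 24 and 7.8% for K = 12.
- Uncorrected sandwich, too small by the factor (K - 2)/K, with z: error = 2P(t on K-2 df > 1.96 × √((K - 2)/K)). For K = 24 the cut-off is 1.877 and the error 7.4%. For K = 12 it is 1.789 and 10.4%.

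**Null simulation.** 24 sites, mean about 56 women, CV 0 to 0.5, ICC 0.02 to 0.12, null rates 48%, 55% and 80%, beta-binomial or logit-normal site effects, 6000 to 8000 runs per setting (Monte Carlo standard error about 0.3 points). There is no true region effect in this table.

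| Test at nominal 5% | 12 v 12 | 6 v 6 or other contrast |
|---|---|---|
| Adjusted chi-square (Donner-Klar or Rao-Scott), 1 df | 5.7-6.8% | 6 v 6: 6.9-8.8% |
| GEE, uncorrected robust SE, z | 6.7-8.7% | 6 v 6: 9.9-12.6% |
| Factorial GEE with interaction, same SE and z | - | simple effect 9.7-11.1%; interaction 8.5-9.6% |
| GEE with region terms, same SE and z | 9-10% (3 regions), about 13% (6 regions) | simple effect 12-15% |

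**When regions really differ.** Randomisation is stratified by region. If region explains 15%, 30% or 50% of the between-site variance and the 12 v 12 test ignores it, the error is about 5-6%, 4-5% or 2-4%. An uncorrected GEE that includes region terms stays at 9-13%.

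**After correction.**

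- Chi-square with a t reference on K - 2 df (equivalently F(1, K-2)): 4.9-5.0%.
- Kauermann-Carroll variance with t, 12 v 12: 4.5-5.7%; with region terms 4.5-5.3%.
- Site-level t-test on 22 df: 4.9-5.5%.

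**The case against.** The best defence is that a condensed article may leave variance corrections and degrees of freedom to the analysis plan, and that a Kauermann-Carroll sandwich is itself a robust variance estimate. This stands for GEE: the uncorrected variance and the z reference are only possibilities that the text leaves open, so the GEE figures are conditional. It does not rescue the normal-approximation sentence, which is a positive statement of an invalid reason. An analysis plan that followed it would carry the error forward.

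Four stronger readings are tempting, and the document does not support them.

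- **That the stated 5% is really about 8%.** The 5% is attached to the chi-square tests, where a main effect runs at about 6-7%. Figures near 8% belong to uncorrected GEE.
- **That the plan defends its GEE intervals by the number of women.** It does not; GEE is brought in for a different reason.
- **That errors of 13-15% are to be expected.** The top of the range needs GEE with region terms and six regions. The protocol gives no number of regions and does not list region as a covariate; its one example is time on ART. Three counties are named, and at least one site per arm in each region caps the number at 24/4 = 6.
- **That every primary p-value is too optimistic.** An unadjusted test can be at or below 5% when regions differ. That would be a chance offset of unknown size and no justification for the method.

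The 6 v 6 contrasts are also not shown to be primary. The sample size is built from two-group totals, which matches the 12 v 12 factorial margins.

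**Conclusion.** The stated justification is wrong and should not support large-sample inference with 24 sites. For the tests it is attached to, the nominal 5% is about 6-7% for a main effect and about 7-9% for 6 v 6. For GEE, only if uncorrected and referred to z, it is about 7-9% for main effects, 9-13% for arm-level or interaction contrasts, and 9-15% with region terms.

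All but the last of these assume no region effect. The last also assumes 3 to 6 regions. The working correlation, the version of the chi-square and the distribution of site effects are assumptions too, varied as shown. For main effects the excess is modest and may vanish under stratification. Severity: should be fixed before analysis.

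**What to change.** Delete the normal-approximation sentence. Refer the cluster-adjusted chi-square to F(1, K-2), where K is the number of sites compared. State that GEE tests and 95% intervals use a small-sample-corrected robust variance, for example Kauermann-Carroll, with a t reference on degrees of freedom based on the sites that inform the contrast. This last point matters for simple effects from the factorial model: in one simulated setting 20 df still gave 6.5%, while the 6 v 6 comparison on 10 df gave 4.9%. A site-level t-test, or a permutation test that respects the stratification, is an acceptable alternative.

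The cost is wording and a software option, with no extra data. Against an uncorrected z interval with equal site sizes, a main-effect interval widens by about 11% (2.074/1.877) and a 6 v 6 interval by about 25% (2.228/1.789).

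Planned power is not at risk. With 1336 women in 24 sites and ICC 0.12, the design effect is 1 + (1.0816 × 55.7 - 1) × 0.12 = 8.11. The standard error of a 12 v 12 difference is √((0.2475 + 0.16) × 8.11/668) = 0.0703 for adherence, and 0.0736 for retention by the same formula. On 22 df, power for the 25-point difference is about 92% and 90%.

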### Data collection and measures

Standardized HIV clinic visit forms and clinic registers developed by the Kenyan Ministry of Health (MOH) are used at all patient clinic visits. For this study, a standardized electronic data abstraction form with built-in quality controls has been developed to capture demographic and clinical information from these clinic and patient records. Data will be collected by trained research staff from source documents on a weekly or bi-weekly basis. All participant visits since the last data abstraction will be entered into the electronic form. Research staff will support accurate and thorough documentation by health care providers during routine site visits. Data collection on study participants will continue for a minimum of 12 months postpartum or until study end.

Primary outcome measures include adherence to ART and retention in care at 12 months postpartum. ART adherence will be measured via self-report routinely collected in the woman’s medical record and viral load. Patient adherence is classified by MOH routine data collection tools as good (>95%), fair (85–94%), or poor (<85%) assessed from the last clinic visit, with clear definitions for each of these categories. Viral load measurements will be conducted as per Kenya National ART guidelines after 6 months of ART for those newly initiating (or at time of pregnancy identification for those already on ART). Those with viral load < 1000 copies/mL will be considered virally suppressed. Those with viral load > 1000 copies/mL will be evaluated for evidence of treatment failure or poor adherence. Our primary outcome for retention in care will be obtained from the women’s clinic visit history and is defined as the proportion of women who have an HIV care visit within 90 days at 12 months after delivery. Data will be shared in agreement with funder (National Institutes of Health, NIH) data sharing policies. Results will be disseminated to local stakeholders (including participants) through local presentations, regional/national/international conferences, and publications.

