## Discussion

This study will determine the impact of long-term (up to 12 months postpartum) text messaging and cMMs on retention in and adherence to ART among pregnant and breastfeeding women living with HIV in Kenya. It will address key gaps in our understanding of what interventions may successfully promote long-term retention in the PMTCT cascade of care. While support among women living with HIV appears to be high for Option B+, high rates of “non-starters” (women who default after first visit) and losses of up to a third of women on ART are concerning [36–39]. The full benefits of Option B+ can only be realized if women are adherent to ART during pregnancy, breastfeeding, and throughout life.

Community-based strategies have the potential to enhance adherence and retention. Most countries in sub-Saharan Africa utilize community or lay health workers to support HIV services. However these workers may or may not be people living with HIV (PLHIV), and the majority are facility-based. While this has its benefits, the WHO and UNAIDS strongly recommend involvement of PLHIV in their own care [40]. Models utilizing PLHIV to support HIV services, such as peer navigators or the Mother-to-Mother program specifically for PMTCT, have shown some benefit but require rigorous evaluation. Our study will be able to determine the separate and combined effectiveness of cMMs and text messages specifically for women on Option B+.

In Kenya, a country of 43 million people, there are currently 37.8 million active mobile phone subscriptions, representing about 88% of the population [41]. While access to a mobile phone is significantly associated with postpartum retention in PMTCT [42–44], there are few studies evaluating the long-term impact of mobile phone technologies on improving long-term retention and adherence in the context of Option B+. One cluster randomized trial of text messages to support PMTCT care in Kenya did not demonstrate increased uptake of PMTCT services such as ART uptake, facility delivery, or infant testing, but it did not study the effects long term [45]. Another recent randomized trial in Kenya used behavior-based text messaging to improve uptake of early infant diagnosis and postnatal retention [23]. Our study will build on the results of this successful trial by using theory-based behavior text messaging to support long-term adherence and retention in the context of Option B+.

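### Two primary outcomes are each tested at a full two-sided 5% for each intervention, with no rule for drawing one conclusion per intervention; if either outcome suffices, the two-sided error per intervention is about 9%

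*Protocol article*

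**What the plan says.** Data collection and measures names the two outcomes: "Primary outcome measures include adherence to ART and retention in care at 12 months postpartum".

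Power and sample size estimation sizes each outcome separately, at 80% power and two-sided p < 0.05: adherence 55% v 80%, retention 48% v 73%. It adds "We powered our study to be able to detect a 25% absolute increase in ART adherence due to each intervention individually" and "This sample size will power us to evaluate both of our primary outcomes".

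Primary analyses describes "comparisons of proportions between intervention and control groups using cluster-adjusted chi square tests", followed by GEE logistic models without and with covariates. On the error rate it says "These tests will be evaluated based on a two-sided alternative hypothesis with a 5% type I error rate".

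The Discussion sets out what is to be concluded: "Our study will be able to determine the separate and combined effectiveness of cMMs and text messages specifically for women on Option B" (the sentence continues with the plus sign of Option B+).

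The article does not say whether an intervention must succeed on one outcome or on both, does not rank the outcomes, and does not divide alpha between them.

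**The concern.** Each intervention gets two full-alpha chances of a significant primary result, and the conclusion that will be read from the trial is about the intervention, not about one test. Suppose adherence gives p = 0.04 and retention shows nothing. Under the text as it stands, that could be reported as a success or as a failure, and the choice would be made after the data are seen. If it is reported as a success, the error rate attached to the conclusion is higher than 5%, even when every single test is exactly valid.

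The unsplit alpha is more than a detail left open for later. It is stated in the text, and the sample size table is built on it, as the working shows.

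**Working it through.** **Inputs from the protocol article.** Two primary outcomes; two-sided alpha 0.05; 80% power; 55% v 80% and 48% v 73%; ICC 0.12; mean cluster size 70, range 50 to 130; 1336 women; 24 sites, six per cell, hence 12 v 12 for each intervention on the factorial margin.

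**Assumptions.** The correlation r between the two test statistics is not given, so a range is shown. The coefficient of variation (CV) of cluster size is not given either; it is taken as range/4 over the mean, (130 − 50)/4 ÷ 70 = 20/70.

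**1. Reproduce the plan's figure.** The formula is the two-proportion sample size with continuity correction, times the design effect DE = 1 + ((1 + CV²) × m − 1) × ICC.

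- DE at m = 70: 1 + (1.0816 × 70 − 1) × 0.12 = 9.966.
- Adherence at alpha 0.05: 53.9 per group, 62 after continuity correction and rounding up. 62 × 9.966 = 617.9, so 618 per group and 1236 in total.
- Retention at alpha 0.05: 58.8 per group, 67 after correction. 67 × 9.966 = 667.7, so 668 per group and 1336 in total.

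Both totals match Table 1 at ICC 0.12, and all 14 rows agree within 2 women. The table therefore rests on a full 0.05 per outcome for one two-group comparison.

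**2. Error rate per intervention if either outcome suffices.** With each test exactly valid, the two-sided rate is P(|Z1| > 1.96 or |Z2| > 1.96). At r = 0 it is 1 − 0.95² = 9.75%. The benefit-only rate is P(Z1 > 1.96 or Z2 > 1.96), which at r = 0 is 1 − 0.975² = 4.94%. Other values come from the bivariate normal distribution.

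| r | Two-sided, any false significant result | Benefit direction only |
|---|---|---|
| 0 | 9.75% | 4.9% |
| 0.3 | 9.5% | 4.8% |
| 0.5 | 9.1% | 4.5% |
| 0.7 | 8.3% | 4.2% |
| 0.9 | 7.0% | 3.5% |

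The reference values are 5% for the first column and 2.5% for the second. At r = 0.5 both are inflated about 1.8 times.

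**3. After the fix.** With no true effect on either outcome, Holm makes an error when the smaller p-value falls below 0.025. That is 1 − 0.975² = 4.94% at r = 0 and less at higher correlation.

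**4. Power at the first Holm step.** With 1336 women in 24 sites, m = 1336/24 = 55.7 and DE = 1 + (1.0816 × 55.7 − 1) × 0.12 = 8.105. The effective size per group is 668/8.105 = 82.4. On the basis of Table 1 (m = 70) it is 668/9.966 = 67.0. Solving the formula of step 1 for power:

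| Outcome | Alpha | 24 sites, mean 55.7 | Table 1 basis, mean 70 |
|---|---|---|---|
| Adherence | 0.05 | 91% | 84% |
| Adherence | 0.025 | 85% | 75% |
| Retention | 0.05 | 89% | 80% |
| Retention | 0.025 | 82% | 71% |

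**The case against.** Four objections have force.

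**The 5% is a per-test level and is right as such.** This stands. The article nowhere claims a 5% rate for an intervention or for the trial, so it states nothing false. The fault is that no level is set for the conclusion.

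**No rule says that either outcome suffices.** This also stands. A reader might infer such a rule from two primary outcomes each tested at 5%, but the article does not define success. If both outcomes had to be significant, the error per intervention would be at most 5% without any split. The 9% is therefore conditional on the either-outcome reading. That reading remains open because neither a joint requirement nor a ranking is written.

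**Multiplicity is usually settled in the SAP, which is not shown.** This is true of the procedure in general and limits how hard the point can be pressed. Here, however, the article itself fixes the alpha and builds the sample size on it: by the same formula, 0.025 per outcome would call for 80 × 9.966, that is 798 per group or 1596 women, for retention. An SAP that shared alpha would depart from the stated basis of the sample size, so the rule belongs beside that statement.

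**The deciding test is not really in doubt.** Primary analyses calls the chi-square comparisons initial and takes the confidence intervals from GEE, which suggests that GEE is the reported analysis. That is a fair reading, and no figure is put here on choosing among tests. Naming one costs nothing.

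**Conclusion.** The point holds as a gap in the decision rule. Each primary outcome is sized and tested at a full two-sided 5% for each intervention, and nothing joins the two results. If either outcome is enough, the two-sided chance of at least one false significant primary result per intervention is about 9%: 7.0% at r = 0.9, 9.1% at 0.5 and 9.75% at 0. These figures assume that each test is exactly valid at 5% and that r lies in the range shown.

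Two stronger readings are tempting and are not supported.

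- A reader might take 9% as the chance of a false claim of benefit. It counts significant results in both directions. For benefit alone the figure is 3.5% to 4.9%, against a nominal 2.5%.
- A reader might multiply over both interventions. With four independent-margin tests the two-sided figure is 1 − 0.95⁴ = 18.5% at r = 0 and about 17% at r = 0.5. The article states no trial-wide error rate, and treating the two interventions of a factorial trial as separate questions, each at 5%, is conventional. The per-intervention figure is the one to act on.

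**What to change.** In Primary analyses, replace the sentence on the type I error rate with wording such as:

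*For each intervention (cMM yes v no; text messages yes v no; 12 v 12 sites on the factorial margin), adherence and retention are tested with the Holm procedure at a two-sided family-wise 5%: the smaller p-value against 0.025 and, if it is significant, the larger against 0.05. The p-values come from [one named test]. The other models and the combined-arm comparisons are supportive and are reported as estimates with 95% confidence intervals.*

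No split across the two interventions is needed. A stated requirement that both outcomes be significant would also control the error; what matters is that one rule is fixed before the data are analysed.

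The change is to wording only, with no more women or sites. The price is power at the first Holm step: about 91% to 85% for adherence and 89% to 82% for retention in the planned 24 sites, at ICC 0.12 with the assumed CV of 20/70 and continuity correction. Both stay above 80%. On the 70-per-site basis of Table 1 they would fall to about 75% and 71%, so the sample size text should say that the margin comes from using 24 sites. If one outcome passes the first step, the other is still tested at 0.05, so the loss is smaller when both truly improve.
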